# Prevention of Early Postoperative Decline (PEaPoD): protocol for a randomized, controlled feasibility trial

**DOI:** 10.1186/s13063-018-3063-z

**Published:** 2018-12-11

**Keywords:** Delirium, Postoperative cognitive decline, Cardiac surgery, Neurocognitive training, Confusion Assessment Method, Montreal Cognitive Assessment

## Abstract

**Background:**

Delirium is associated with a significantly increased risk of postoperative morbidity and mortality. Furthermore, delirium has been associated with an increased risk of prolonged cognitive deficits and accelerated long-term cognitive decline. To date, experimental interventions for delirium have mainly focused on alternative pharmacologic and behavioral strategies in the postoperative period. Few studies have examined whether proactive strategies started *before* surgery can prevent delirium or reduce its sequelae. Neurocognitive training programs such as Lumosity have been shown to be effective in increasing cognitive performance in both elderly healthy volunteers and patients suffering from a myriad of acute and chronic medical conditions. When initiated in the preoperative period, such training programs may serve as interesting and novel patient-led interventions for the prevention of delirium and postoperative cognitive decline (POCD). We hypothesize that perioperative neurocognitive training is feasible in the older cardiac surgical population and are testing this hypothesis using a randomized controlled design.

**Methods:**

The Prevention of Early Postoperative Decline (PEaPoD) study is a randomized, controlled trial with a target enrollment of 45 elderly cardiac surgical patients. Subjects will be randomized in a 1:1 ratio to undergo either at least 10 days of preoperative neurocognitive training, continued for 4 weeks postoperatively, or usual care control. The primary outcome, feasibility, will be assessed by study recruitment and adherence to protocol. Secondary outcomes will include potential differences in the incidence of postoperative in-hospital delirium and POCD up to 6 months, as determined by the Confusion Assessment Method and the Montreal Cognitive Assessment.

**Discussion:**

PEaPoD will be the first trial investigating the use of perioperative cognitive training to potentially reduce delirium and POCD in the cardiac surgical population. Information gleaned from this feasibility study will prove valuable in designing future efficacy studies aimed at determining whether this low-risk, patient-led intervention can reduce serious postoperative morbidity.

**Trial registration:**

ClinicalTrials.gov, NCT02908464. Registered on 21 September 2016.

**Electronic supplementary material:**

The online version of this article (10.1186/s13063-018-3063-z) contains supplementary material, which is available to authorized users.

## Background

Characterized by altered consciousness, disorientation, and inattention, delirium is associated with an increased incidence of postoperative complications, prolonged hospital length of stay, and greater in-hospital mortality [1]. The highest reported incidence of postoperative delirium is in those undergoing cardiac surgery, with nearly 200,000 patients per year in the USA experiencing this morbid condition during their hospital admission [2]. While classically defined as a temporary condition, recent data has demonstrated that many patients with delirium can experience long-lasting effects on their cognitive performance and an accelerated rate of long-term cognitive decline [1, 2]. Defined by persistent deficits in memory and executive function, postoperative cognitive decline (POCD) can be detected in roughly 30% of patients 6 months after the day of their operation [3, 4]. Given an aging population’s projected increasing demand for cardiac surgery and the significant impact of delirium and POCD on postoperative recovery, a simple, effective, low-risk intervention to reduce their incidence would be invaluable [5]. Numerous investigations have tested various strategies to prevent postoperative delirium and cognitive dysfunction, largely focusing on pharmacologic interventions, with varying degrees of success [6]. On the other hand, non-pharmacologic strategies such as the Hospital Elder Life Program (HELP) have shown consistent benefit in reducing the incidence of delirium and have gained widespread acceptance, particularly in medical patients [7]. Although HELP includes guidelines for a perioperative regimen that includes frequent cognitive stimulation, at this time there has not been a consensus as to the most effective modality.

In an effort to reproduce the gains observed with physical prehabilitation in improving postoperative functional recovery, clinicians and researchers have begun to consider cognitive prehabilitation’s potential to maximize recovery following major surgery [8, 9]. For example, preclinical data has demonstrated that preoperative cognitive enrichment can reduce perioperative neuronal inflammation and POCD in rats [10]. Additionally, data from observational studies in humans suggests that preoperative participation in cognitively stimulating activities is associated with a reduced incidence and severity of postoperative delirium [11]. Given these findings, it would follow that modalities that can potentially improve cognitive performance or build reserve in domains commonly affected by surgical exposure would serve as ideal candidate interventions for clinical trials evaluating their potential benefit in the older surgical population.

For adults over 60 years of age, normal aging is associated with declining cognitive ability, particularly in the executive functions of the prefrontal cortex, including attention, working memory, and processing speed [12]. Building on existing data suggesting improvement in these domains after video game use in young adults, there has been a push to develop interactive software aimed at similarly improving cognitive performance in older adults [13]. To date, multiple interactive platforms have emerged which package rigorous attention and memory tasks within engaging and entertaining gaming programs, and many have shown encouraging early results. For example, results of a secondary analysis of the data from the Advanced Cognitive Training for Independent and Vital Elderly (ACTIVE) trial suggest that the use of computerized brain training games can reduce the incidence and slow the onset of age-related dementia [14].

Lumosity, a commercially available neurocognitive gaming platform, has a promising early track record of improving cognitive performance in older adults. In a prospective randomized trial, training with Lumosity has been shown to reduce distraction and increase alertness, and it has been associated with significantly better performance on attention and both immediate and delayed visual memory tasks compared to controls [15, 16]. Additionally, when compared to an active control group, participants in another randomized controlled trial were found to have significantly greater improvements in speed of processing, short-term memory, working memory, problem solving, and fluid reasoning assessments [17]. Furthermore, as many of the same deficits found in age-related cognitive decline are present in both acute and chronic medical conditions, investigators have expanded the use of related neurocognitive training programs to rehabilitate cognitive dysfunction arising in numerous patient subgroups, including those with traumatic brain injury, stroke, and heart failure [18, 19]. Unlike these physical conditions, perioperative delirium and POCD occur with a known and predictable onset, making them amenable to preventive strategies. Therefore, the preoperative period provides an attractive target for a prehabilitative strategy to reduce the impact of these morbid conditions.

Despite promising preliminary data from allied fields, the concept of neurocognitive training in the perioperative period has not yet been investigated. The objective of this study is to determine the feasibility of using a perioperative neurocognitive training program in the cardiac surgical population. Data obtained through the conduct of this study will prove critical to the design and implementation of future protocols evaluating the potential efficacy of neurocognitive training to prevent postoperative delirium and POCD.

## Methods and design

### Study design

The Prevention of Early Postoperative Decline (PEaPoD) study is a randomized, controlled, single-center, assessor-blinded clinical trial of eligible older adult cardiac surgical patients. Subjects will be randomized in a 1:1 allocation to either perioperative neurocognitive training or usual care control. The primary outcome of feasibility will be determined based on enrollment and protocol adherence. Secondary outcomes, including the incidence of postoperative delirium and POCD, will be evaluated using the Confusion Assessment Method (CAM) and the Montreal Cognitive Assessment (MoCA) respectively. Additionally, patients will be followed until 6 months postoperatively and evaluated via a telephonic MoCA (t-MoCA) to assess the presence of long-term POCD and to map the trajectory of return to baseline cognitive function. A study schema is provided in Fig. 1. Our study protocol was written according to the principles outlined in the Standard Protocol Items: Recommendations for Interventional Trials (SPIRIT) checklist (Fig. 2, Additional file 1) [20].

**Fig. 1 Fig1:**
[figure not shown]
Study schema

**Fig. 2 Fig2:**
[figure not shown]
Standard Protocol Items: Recommendations for Interventional Trials reporting of study enrollment, interventions, and assessments

### Setting

This study will be conducted at the Beth Israel Deaconess Medical Center (BIDMC) in Boston. BIDMC is a 700-bed tertiary care hospital academically affiliated with the Harvard Medical School. More than 900 open-heart procedures with cardiopulmonary bypass (CPB) are performed at BIDMC per year.

### Study registration

Institutional Review Board (IRB) approval was obtained, and oversight of the study by the BIDMC’s Committee on Clinical Investigations is currently ongoing under IRB #2016P000145. PEaPoD was registered with the identifier NCT02908464 on the National Institutes of Health (NIH) ClinicalTrials.gov website on 21 September 2016. Once the trial is completed, results will be reported according to the Consolidated Standards of Reporting Trials (CONSORT) guidelines and the SPIRIT checklist (Additional file 1) [20, 21]. The trial is active and ongoing, and any amendments made to the protocol are reported to and approved by the BIDMC IRB.

### Inclusion criteria

Patients will be deemed eligible for enrollment if they are between the ages of 60 and 90, are scheduled to undergo cardiac surgery at least 10 days after enrollment, and have obtained an educational level of at least high school or equivalent. The educational level requirement was chosen to help screen out pre-exisiting cognitive deficits and attempt to homogenize the baseline cogntive abilities of the study population. As neurocognitive training with Lumosity is thought to be most effective with greater training times, we chose a minimum of 10 days of lead-in time as an appropriate cutoff to balance the interests of an effective intervention with scheduling demands for cardiac surgery, which frequently dictate short preoperative wait times.

### Exclusion criteria

Patients will be excluded for a history of pre-existing psychiatric illness such as anxiety or depression, stroke, dementia, epilepsy, Parkinson’s disease, or other forms of cognitive decline. Due to the nature of the study intervention, non-English speaking patients and those with significant visual impairment will also be excluded.

### Dropout criteria

After obtaining consent, blinded study investigators will perform a baseline MoCA with the patient. Patients with a score of less than 10 (indicating severe baseline cognitive impairment) will be withdrawn from the study.

### Study intervention: neurocognitive training

Patients will be randomized in a 1:1 allocation via a concealed block scheme to either intervention or control using the Research Electronic Data Capture (REDCap) randomization feature. Patients randomized to the intervention group will be asked to complete two 15-min neurocognitive training sessions per day, from the day of enrollment until 4 weeks after their day of surgery including the immediate postoperative in-hospital period. Our inclusion criteria were designed so that study participants with at least 10 days of lead-in time could then complete at least 5 h of training before surgery, with the understanding that there may be unequal durations of gameplay based on scheduling patterns among patients. The training instrument used in this study, Lumosity, was created by Lumos Labs Inc., San Francisco, CA, USA, as a web-based and mobile platform designed to improve performance in specific cognitive abilities through interactive gameplay. As part of a customized training program tailored towards cognitive abilities thought to be deficient in the postoperative period, patients in the intervention arm will train in each of the following categories per session: memory, attention, problem solving, flexibility, and processing speed. Participants in the intervention arm will be given a study iPad that is WiFi enabled and locked to the Lumosity program. Adherence to the study protocol will be quantified using automated gameplay data received from Lumos Labs. Unblinded study members will be responsible for providing technical support to participants as needed and for periodic checks on adherence between in-person assessments.

### Control arm: usual care

Patients randomized to the control group will undergo the usual standard of care for cardiac surgical procedures, which currently does not consist of a perioperative neurocognitive training regimen. Instead of using an active control group as is common for the evaluation of the efficacy of a cognitive training instrument, the investigators thought that the assignment of a usual care control was more appropriate in this setting, as it is representative of a standard of care that currently lacks specific recommendations for cognitive activities in the perioperative period. Patients in the control arm will be asked to refrain from obtaining a Lumosity account to reduce any potential contamination with the intervention arm.

#### Study outcomes

##### Primary outcome: feasibility

To best evaluate the potential effect of a neurocognitive training program on the development of postoperative delirium and POCD, a large randomized controlled trial would need to be performed. However, before undertaking such a trial, it is imperative to show that implementation of a prehabilitative program is feasible. This is especially true given the heavy reliance on a patient-performed intervention and need for recruitment of interested subjects with sufficient lead-in time for the intervention to be effective. Furthermore, since this is the first time neurocognitive training will be implemented in this setting, there is no preliminary data regarding a potential effect size for an accurate power calculation to be performed. Therefore, the PEaPoD trial was designed to evaluate feasibility as a primary outcome. Feasibility will be assessed through both recruitment and adherence. Satisfactory recruitment will be defined as enrollment of 50% or more of eligible patients, which will reflect efficient screening and approach procedures and also sufficient interest within this patient population. Adherence will be quantified for analysis using automated gameplay data recorded during use. Consideration of three separate training periods (preoperative, immediate postoperative, and extended postoperative periods) will be taken into account in evaluating optimal adherence patterns for potential future study.

##### Secondary outcomes: postoperative delirium and POCD

Additional information will be obtained to inform future investigations. The incidence of postoperative delirium will be evaluated in both groups through the use of the CAM, the current standard for the diagnosis of delirium in clinical research studies [22]. Assessments will be conducted by study members blinded to group assignment on each postoperative day until the day of hospital discharge, or day seven, whichever comes first. In the event that a study patient is still intubated and/or is unable to speak, the CAM-ICU, a variation of the CAM that does not require verbal responses, will be used. Patients who refuse assessments will be approached again within a few hours, but they will not be coded as delirious for that day if the exam cannot be completed. Blinded team members have been extensively trained in the administration of the CAM by the group responsible for the creation of the long CAM assessment as part of a larger collaboration within the departments of Anesthesia and Medicine at BIDMC. Scoring of CAM assessments will be informed by the performance on basic cognitive tasks (immediate and delayed recall, orientation, abstraction, and attention), the Delirium Symptom Interview (DSI), and a daily pain assessment. Acute changes in performance in these cognitive areas will be compared to performance on baseline MoCA testing for reference. The occurrence of POCD will be evaluated using the MoCA, a diagnostic instrument designed to detect mild cogntiive impairment and dementia with a high degree of sensitivity and specificity [23]. The full MoCA has three distinct versions, each of which will be used in the course of the study to minimize the impact of learning on test performance. A baseline MoCA will be performed on the day of enrollment, followed by an additional assessment using a different version that will take place before surgery on the day of the patient’s operation. The additional preoperative assessment will allow for identification of any changes in performance that could be potentially attributable to neurocognitive training as well as identification of an updated cognitive baseline. A third MoCA will be administered on the day of hospital discharge, again using a new test version. Additionally, a t-MoCA will be administered at 1, 3, and 6 months postoperatively to track any long-term postoperative cognitive deficits or time of return to baseline cognitive performance. The t-MoCA contains all of the components of the full MoCA with the exception of the questions requiring visual cues or drawing, and scores between the two tests can be normalized for comparison [24]. In lieu of using the t-MoCA throughout the study for consistency, we believe that the use of the full MoCA where possible may be more sensitive to mild cognitive impairment, as it contains more testing categories and could potentially identify issues with impaired visuospatial tasks. Our protocol will allow for assessment windows of 7 days for the 1 month follow-up and 14 days for the 3 and 6 months follow-up t-MoCAs. As for the CAM, all cognitive assessments will be administered and scored by trained study team members blinded to the subject’s group assignment.

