#### Statistical analysis

##### Sample size calculation

A convenience sample of 45 patients will be chosen to assess the feasibility of perioperative neurocognitive training. A total of 20 enrolled and randomized subjects are needed per group to assess the rates of participation, adherence, and dropout associated with the study. To account for patients who may fail the initial MOCA screen or withdraw, we have added five patients to the desired enrollment sample size for a total planned enrollment of 45 patients.

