##### Analysis of secondary outcomes

Differences in the incidence of postoperative delirium and POCD will be presented as proportions and assessed with the use of a chi-square test. Odds ratios and 95% confidence intervals will be generated using logistic regression and interpreted. A parametric *t* test or non-parametric equivalent will be utilized to identify differences in POCD (MoCA scores) at each time point, controlling for baseline cognitive function. To account for the multiple measurements per subject, we will employ repeated measures regression techniques (e.g., analysis of variance). Although randomization should eliminate baseline confounders, univariate and multivariable logistic and linear regression modeling may be employed to assess the relationship between preoperative Lumosity use and both delirium and POCD, adjusting for any differences that may persist between groups.

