In addition to these limitations, a potential source of bias in our study is the possibility for our assessors to become unblinded to group assignment throughout the course of a 6-month study period. We have taken many steps to prevent this occurrence and have systems in place to manage unblinding if it does occur. Throughout the course of the study, unblinded investigators will reiterate the importance of maintaining the blind, including detailed conversations both at the time of consent and prior to blinded study interactions (e.g., in-hospital cognitive assessments) on how to avoid potential conversations regarding the use of a mobile device in general. In an effort to maintain consistency, clearly defined roles have been delineated within the research group, with two unblinded team members solely responsible for monitoring adherence and technical support who are never involved in the assessment process. If an assessor does become unblinded, an alternate blinded team member trained in administering the CAM and MoCA is made available. If an alternate blinded team member is not available, the assessment is not performed and will be treated as missing data.

To summarize, elderly patients undergoing cardiac surgery have the highest incidence of postoperative delirium and POCD, which places them at an elevated risk for significantly higher perioperative morbidity and long-lasting detrimental effects on cognition. Neurocognitive training has been shown in preliminary studies to be effective in improving cognitive performance in the areas thought to be affected in the postoperative period. PEaPoD will be the first study to investigate the use of perioperative neurocognitive training in this high-risk patient population. Through the performance of this study, valuable information will be obtained that will guide future studies that are well designed to examine the technique’s efficacy in preventing postoperative delirium and POCD.

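### The coding rule for refused CAM days can only lower the recorded delirium incidence, by an amount the protocol cannot fix

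*Protocol article*

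**What the plan says.** Under the heading on secondary outcomes (postoperative delirium and POCD), blinded staff administer the CAM "on each postoperative day until the day of hospital discharge, or day seven, whichever comes first", so a patient has at most seven daily assessments. If the patient is intubated or cannot speak, "the CAM-ICU, a variation of the CAM that does not require verbal responses, will be used". For patients who refuse, the team tries again within a few hours, but "they will not be coded as delirious for that day if the exam cannot be completed".

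The Discussion deals with a different kind of missed assessment. If an assessor has become unblinded and no blinded alternate is available, "the assessment is not performed and will be treated as missing data".

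The section on analysis of secondary outcomes states: "Differences in the incidence of postoperative delirium and POCD will be presented as proportions and assessed with the use of a chi-square test". It adds odds ratios from logistic regression and does not mention refused days. The Discussion also says that the trial should yield an effect size for powering later, larger studies.

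**The concern.** A refused day and a day skipped for lack of a blinded assessor both leave no CAM result. One is declared missing. The other carries an instruction that works in one direction only. The Background describes delirium as "Characterized by altered consciousness, disorientation, and inattention", and a patient in that state may well decline or fail to finish an examination. Refusal is therefore plausibly more common on delirious days.

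A patient whose every delirious day is refused enters the analysis as never delirious. The resulting incidence would be too low, and so would the control-arm rate taken forward to plan an efficacy trial.

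**Working it through.** **Figures in the document.** The only computed figure is the sample size. "A total of 20 enrolled and randomized subjects are needed per group", and "we have added five patients to the desired enrollment sample size for a total planned enrollment of 45 patients": 2 × 20 + 5 = 45, which reproduces. The bias does not depend on it. No in-hospital delirium rate, delirium duration or refusal rate is given. The Background's figure of roughly 30% is for POCD at 6 months, so the 30% used below is an assumption.

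**Direction.** Let p be the incidence (at least one positive day) that complete CAM testing would have recorded. Let m be the share of those patients whose every delirious day was refused. The rule never creates a positive day, so

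recorded incidence = p(1 − m) ≤ p.

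**Size.** With d delirious days per patient and independent refusal probability r on each, m = r^d. At an assumed p = 0.30:

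| r | d = 1 | d = 2 | d = 3 |
|---|---|---|---|
| 0.20 | 0.30 × (1 − 0.200) = 24.0% | 0.30 × (1 − 0.040) = 28.8% | 0.30 × (1 − 0.008) = 29.8% |
| 0.40 | 0.30 × (1 − 0.400) = 18.0% | 0.30 × (1 − 0.160) = 25.2% | 0.30 × (1 − 0.064) = 28.1% |

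The relative loss is m whatever the value of p. Over assumed ranges of r from 0.05 to 0.40 and d from 1 to 3, it runs from about 0% (0.05³) to 40%. With p between 0.20 and 0.50, the largest absolute loss is 0.50 × 0.40 = 20 points. If refusals cluster completely, so that a patient refuses either every delirious day or none, then m = r for any duration and the d = 1 column applies throughout.

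With 20 patients per arm, each delirious patient lost in this way lowers that arm's rate by 1/20 = 5 points.

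**Comparison of arms.** With no true effect and the same m in both arms, the odds ratio stays at 1.00. If m differs, it moves. At p = 0.30, take m = 0 under training and 0.20 under control. The recorded rates are 30% and 24%, and the odds ratio is (0.30/0.70)/(0.24/0.76) = 1.36. The reverse gives 0.74.

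**Does recoding to missing cure it?** Not alone. A patient with no positive CAM who stays in the denominator adds nothing to the numerator, whether the refused day is negative or missing.

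Dropping every patient who has an unassessed day and no positive CAM errs the other way. Suppose refusal is 5% on non-delirious days, over seven days. The share of never-delirious patients with at least one refusal is 1 − 0.95⁷ = 0.302. At p = 0.30, r = 0.20 and d = 1, the complete-case incidence is 0.24/(0.24 + 0.70 × 0.698) = 32.9%. For d = 2 and 3 it is 37.1% and 37.8%.

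Counting every unresolved refusal day as delirious would give 0.30 + 0.70 × 0.302 = 51.1% under the same assumptions. That is an upper bound, not an estimate.

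**The case against.** Several points on the other side are sound.

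- A reader might infer that the refusal rule and the unblinding rule contradict each other. They do not. One covers a patient who refuses, the other an assessment the team chooses not to perform. The approaches are inconsistent, but both rules can be followed.
- The wording does not say outright that a refused day is negative. It may mean only that refusal is not itself scored as positive. The text should settle this, but the recorded incidence is the same on either reading while the patient stays in the denominator.
- Re-approach within hours, daily testing and the CAM-ICU all limit the loss. For delirium lasting three days with independent refusals it is at most about 2 points in the table above.
- A reader might infer that two daily training sessions make refusal more likely in that arm and so bias the comparison. Nothing in the document links training to CAM refusal.
- Delirium is a secondary outcome, and the protocol says that the trial is not powered for clinical outcomes. At 30% incidence and 20 per arm, the standard error of one arm's rate is √(0.30 × 0.70/20), about 10 points, which exceeds most of the illustrated losses.

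Sampling error, however, is visible in a confidence interval, while a one-way coding error is not. Missing-data methods can often be left to an analysis plan. Here the article itself states a coding rule with a known direction.

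**Conclusion.** The point holds as a one-way coding rule that can only lower the recorded incidence of delirium. Its size cannot be fixed from the document. At an assumed 30% incidence with independent refusals, the loss runs from 0.2 points (20% refusal, three days) to 12 points (40% refusal, one day). Clustered refusals would make it larger for longer episodes. That refusal is related to delirium is plausible on the protocol's own description but not quantified.

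The documents do not support a claim of contradictory rules, of bias between arms, or that declaring refused days missing would by itself repair the estimate. The primary feasibility conclusion is untouched. What is affected is the delirium rate that later studies would plan on.

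**What to change.** - Replace the rule with a code of not assessed for any refused or uncompleted day, and record the reason. Use the same code for days skipped because no blinded assessor was available.
- Report assessable days and refused days by arm beside the delirium proportions.
- Pre-specify two sensitivity analyses: (a) unresolved refusal days counted as delirious; (b) patients with an unassessed day and no positive CAM treated as having a missing outcome, handled by bounds or multiple imputation and not by simple exclusion.

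The cost is one reason code and two short tables, with no extra visits or tests.

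### The day-of-surgery MoCA, taken after randomised training has begun, is labelled an updated baseline, and the POCD analysis does not say which baseline it uses

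*Protocol article*

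**What the plan says.** All references are to the protocol article.

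- **Two preoperative scores.** Under *Secondary outcomes: postoperative delirium and POCD*: "A baseline MoCA will be performed on the day of enrollment". A second test, in a different version, is to "take place before surgery on the day of the patient’s operation".
- **Two roles for the second score.** The same section says it will allow "identification of any changes in performance that could be potentially attributable to neurocognitive training", "as well as identification of an updated cognitive baseline".
- **Training lies between them.** *Study intervention: neurocognitive training* runs the sessions "from the day of enrollment until 4 weeks after their day of surgery" and plans so that patients with "at least 10 days of lead-in time could then complete at least 5 h of training before surgery". *Control arm: usual care* describes care "which currently does not consist of a perioperative neurocognitive training regimen".
- **The analysis.** *Analysis of secondary outcomes* compares POCD incidence as proportions and MoCA scores "at each time point, controlling for baseline cognitive function". The secondary outcomes section also tracks the time at which patients return to baseline on the telephone MoCA. Neither place says which preoperative score is the baseline.
- **Use of the result.** The *Discussion* expects the trial to supply an effect-size estimate for powering larger studies.

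**The concern.** A baseline for comparing randomised arms should be a measurement that treatment cannot have altered. The day-of-surgery MoCA follows at least 10 days of training in one arm only, and the article itself looks to it for a training effect. For the comparison between arms it is therefore a post-randomisation outcome. Its two stated roles do not fit together there: a score that may carry the treatment effect cannot also be the neutral reference.

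The word *updated* invites an analyst to let the later score replace the earlier one. If that happened, the better the training worked before surgery, the higher the bar the trained arm would have to meet afterwards. A real postoperative benefit could be hidden, or a harm reported where none exists. With two scores carrying the name baseline, the choice could also be made after the data are seen, and it could change the sign of the result.

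**Working it through.** **The plan's own figures.** Preoperative training: 10 days × 2 sessions × 15 min = 300 min = 5 h, as stated. Enrolment: 2 × 20 + 5 = 45, as stated. Neither is in dispute.

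**Order of events.** Enrolment MoCA → training in one arm, at least 10 days → day-of-surgery MoCA → operation → postoperative MoCAs. I take the enrolment MoCA to precede the first session, because the article places it after consent and treats it as a screen (*Dropout criteria*; *Sample size calculation*).

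**Algebra.** Let *g* be the training effect on the day-of-surgery score and *h* the training effect on a postoperative score.

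- Difference in change from enrolment: *h*.
- Difference in change from day of surgery: *h* − *g*.
- Difference adjusted for the day-of-surgery score: *h* − *b·g*, where *b* is the within-arm slope of the postoperative score on that score.

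The shift of −*g* needs no numerical assumption. If *g* = 0, every version gives *h*.

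**Illustration.** None of these inputs comes from the documents: MoCA SD 3, reliability 0.75, mean surgical decline 1 point (SD 1.5), POCD counted as a fall of 2 or more points.

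- SD of change = √(2 × 9 × 0.25 + 1.5²) = √6.75 = 2.60.
- Slope *b* = 0.75.
- Controls, either baseline: Φ((−2 + 1)/2.60) = 35%.
- Trained arm with mean change −2: Φ(0) = 50%.
- Trained arm with mean change 0: Φ(−2/2.60) = 22%.

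A simulation with 400,000 patients per arm gave:

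| *g*, *h* | Reference | Change difference | Adjusted difference | POCD control v trained | OR |
|---|---|---|---|---|---|
| 1, 0 | enrolment | 0.0 | 0.0 | 35% v 35% | 1.00 |
| 1, 0 | day of surgery | −1.0 | −0.75 | 35% v 50% | 1.86 |
| 1, 1 | enrolment | +1.0 | +1.0 | 35% v 22% | 0.52 |
| 1, 1 | day of surgery | 0.0 | +0.26 | 35% v 35% | 0.99 |
| 2, 1 | enrolment | +1.0 | +1.0 | 35% v 22% | 0.53 |
| 2, 1 | day of surgery | −1.0 | −0.50 | 35% v 50% | 1.85 |
| 0, 1 | day of surgery | +1.0 | +1.0 | 35% v 22% | 0.53 |

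**Other assumptions, same direction.** Take a threshold of 3 points, mean decline 1, SD of change 2 to 3, *g* = 1 and *h* = 0. Controls: 1 − Φ(2/SD) = 16% to 25%. Trained arm, day-of-surgery reference: 1 − Φ(1/SD) = 31% to 37%. OR 2.37 down to 1.73.

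**At the planned size.** With *h* = 0, 20 per arm and a two-sided 5% test on change from day of surgery, the rejection probability for MoCA SD 3 and *g* = 1 is about Φ(1/(2.60 × √(2/20)) − 1.96) = Φ(1.22 − 1.96) ≈ 23%. Over MoCA SD 2.5 to 3.5 it is 19% to 28% for *g* = 1 and 59% to 78% for *g* = 2.

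**The case against.** **No sentence commits to the harmful use.** This stands. The article uses the term baseline MoCA for the enrolment test, and its remark on an updated baseline says what the measurement permits, not how it will be analysed. Reading the analysis section as meaning the enrolment score is natural. A reader might infer that the POCD comparison will be made from the day-of-surgery score and is therefore biased; the text does not say so. It does not exclude it either, and the label is stated in the very section that describes how POCD is evaluated. An analysis plan that followed it would carry the error forward.

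**The size of fall that counts as POCD is not given.** A reader might count this as a further fault. It is detail that an analysis plan or full protocol commonly holds, and the point here does not depend on it.

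**The later score has a proper use.** This stands in part. The waiting time before surgery varies, and a score just before the operation separates change before surgery from change across it. But *h* − *g* answers a different question from the effect of the whole perioperative programme on postoperative cognition.

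**Adjustment does not remove the whole benefit.** Correct: in the illustration about a quarter of a fully kept gain survives. Only change scores subtract all of it.

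**The magnitudes are assumed, and false harm needs the gain to vanish.** Also correct. Training continues for 4 weeks after surgery, so a complete loss is a strong assumption at discharge and 1 month, less so at 3 and 6 months. If the gain is kept, however, the error is a hidden benefit.

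**POCD is secondary and the trial is small.** The article says it is not powered for clinical outcomes. For example, 4/20 v 7/20 gives OR (7 × 16)/(13 × 4) = 2.15 with a 95% interval of about 0.5 to 9.0, which covers 1 and the whole 1.7 to 2.4 range. This limits the severity. It does not cure the bias, which a larger sample would not remove.

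**Conclusion.** The point holds as an ambiguous baseline that permits a biased analysis, not as proof that one is planned. The article gives a post-randomisation score the name of a baseline and leaves two later references to baseline unassigned. If the day-of-surgery score were the between-arm reference, the change-score difference would be wrong by exactly −*g*, and the adjusted difference by −*b·g* (three quarters of *g* under the assumed reliability). The direction is against training whenever training raises the score. The percentages and odds ratios rest wholly on the assumptions listed; the −*g* shift does not. With *g* = 0 there is no bias.

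The severity is moderate. The primary feasibility outcome and the sample size are untouched. What is exposed is the secondary POCD estimate, which the *Discussion* intends for powering later trials.

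**What to change.** 1. State that the enrolment MoCA, taken before any training session, is the baseline for every between-arm POCD definition, covariate adjustment and return-to-baseline comparison.
2. Analyse the day-of-surgery MoCA as an outcome: the effect of preoperative training.
3. Limit change from the day-of-surgery score to description within each arm, or to an analysis labelled exploratory.
4. Drop or reword the updated-baseline label to match.

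The POCD threshold can stay with the analysis plan. The cost is wording only: both scores are already collected, and no visit, test or patient is added. The change should be made before the data are analysed.
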